**Fig. 2 Fig2:**
[figure not shown]
Proposed flow of participants

### Sample size

The most updated meta-analysis of 28 self-help CBT-I RCTs [19] showed a significant treatment effect in alleviating depressive symptoms (Hedges’ *g* = 0.35) and insomnia symptoms (Hedges’ *g* = 0.79). It also found that the mean cumulative study attrition rates were 21.25% (SD = 15.31%) and 18.4% (SD = 18.21%) in the treatment and the waiting list/routine care/no treatment/psychoeducation groups, respectively. Hence, a conservative small effect size (Cohen’s *f* = 0.2) and an attrition rate of 30% are estimated for the present study.

The sample size calculation for each of the three primary outcomes (i.e., insomnia severity, poor sleep quality, and depression severity) is based on mixed ANCOVA using GPower 3.1. To conduct a 2 (condition: CBT-I versus waitlist control) × 2 (assessment: baseline versus post-intervention) mixed ANCOVA with an alpha value set at 0.05, two-sided, 80% power to detect a small effect of 0.2 (Cohen’s *f*) between two groups while controlling for 12 covariates (demographics, clinical comorbidity, treatment expectancy, and acceptability of treatment), a total sample size of 199 will be required. In order to account for 30% attrition, a total sample of 285 participants will be sufficient to detect a small effect size (Cohen’s *f* = 0.2) for the difference in the change in each of the three primary outcomes (i.e., insomnia severity, poor sleep quality, and depression severity) from baseline to post-intervention between CBT-I condition and waitlist control condition with a two-sided 5% significance level and a power of 80%.

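### The planning effect f = 0.2 (d = 0.40) is called conservative but exceeds the cited depression effect (g = 0.35); at that effect, power on the protocol's own basis is about 69%

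*Protocol article*

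**What the plan says.** In the protocol article, the Sample size section opens with a meta-analysis of 28 self-help CBT-I trials. For depression it "showed a significant treatment effect in alleviating depressive symptoms (Hedges’ *g* = 0.35"; for "insomnia symptoms (Hedges’ *g* = 0.79". No effect on sleep quality is given there. The text also reports mean attrition of 21.25% in treated groups and 18.4% in control groups.

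The planning value is then presented as following from these figures: "Hence, a conservative small effect size", with Cohen's f = 0.2 and 30% attrition. One calculation serves all outcomes ("The sample size calculation for each of the three primary outcomes", depression severity among them). The method is a "mixed ANCOVA with an alpha value set at 0.05, two-sided, 80% power to detect a small effect of 0.2", "while controlling for 12 covariates (demographics, clinical comorbidity, treatment expectancy, and acceptability of treatment". The result is 199 evaluable and 285 randomised, said to suffice for each primary outcome "with a two-sided 5% significance level and a power of 80"%. No covariate R-squared or baseline-to-post correlation is stated.

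**The concern.** A planning effect is conservative against a body of evidence when it is smaller than the effect that the evidence shows. Here two cited effects are followed by a single planning value on a different scale (f rather than g), and the change of scale hides the comparison. Put on one scale, the planning value lies well below the insomnia effect and above the depression effect.

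Depression severity is one of three primary outcomes, and the trial enrols people with major depression. A reader who accepts the paragraph will believe that the cited depression effect is covered at 80% power with room to spare. If the depression comparison turns out non-significant, that belief makes the result look like stronger evidence of no effect than it is.

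**Working it through.** **Inputs.** All from the Sample size section unless noted: f = 0.2; g = 0.35 (depression) and 0.79 (insomnia); alpha 0.05 two-sided; 12 covariates; 199 evaluable; 30% attrition; 1:1 allocation (Trial design). I read the pooled g as the standardised between-group difference d.

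**1. Reproduce the plan's figure.** ANCOVA power from the noncentral F distribution with numerator df = 1, denominator df = N − 2 − 12 and noncentrality λ = f²N.
- At N = 199, f = 0.2: df = 185, λ = 0.04 × 199 = 7.96, power 80.1%. At N = 198 it is 79.9%, so 199 is the smallest N.
- 199 / 0.70 = 284.3, rounded up to 285.

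Both figures reproduce exactly. The repeated-measures routines do not give 199: for correlations of 0.3 to 0.7 the within-between version needs 32 to 71 and the between version 130 to 169. The stated N therefore comes from the ANCOVA routine, in which f = d/2 for two equal groups, and it contains no built-in gain from within-person correlation.

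**2. Put the effects on one scale.**

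| | d or g | f = d/2 |
|---|---|---|
| Planning value | 0.40 | 0.200 |
| Cited, depression | 0.35 | 0.175 |
| Cited, insomnia | 0.79 | 0.395 |
| Cited, sleep quality | none | – |

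0.40 / 0.35 = 1.14, so the planning value is 14% above the cited depression effect.

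**3. Power at the cited effects, N = 199, alpha 0.05, no variance explained by covariates.**
- Depression: λ = 0.175² × 199 = 6.09, power 69.0%. A normal approximation with 99.5 per arm gives 69.5%.
- Insomnia: power above 99.9%.
- For scale only: 80% at f = 0.175 corresponds to 259 evaluable, and 259 / 0.70 = 370 randomised.

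**4. Sensitivity for depression at alpha 0.05.**

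Evaluable N, with no variance reduction:
- 199 (30% attrition): 69%
- about 228 (mean of the two cited attrition rates, 19.8%; 285 × 0.802): 75%
- all 285: 84%

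Variance reduction at N = 199; the correlations are assumptions, because the article gives none:

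| Correlation | 0.3 | 0.5 | 0.7 |
|---|---|---|---|
| Baseline always adjusted for, f = 0.175 / √(1 − r²) | 73% | 81% | 93% |
| Change score, f = 0.175 / √(2(1 − r)) | 55% | 69% | 89% |

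The cited depression effect becomes f = 0.2 at r = √(1 − (0.175/0.2)²) = 0.48 with baseline adjustment, or at r = 1 − (0.175/0.2)²/2 = 0.62 with a change score.

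**The case against.** The strongest reply is that the power statement is true as made. The section claims 80% at f = 0.2, not at g = 0.35, and its arithmetic is right. A reader might infer that the trial's 80% is wrong and should read 69%; the document does not support that. What fails is the step from the evidence to the planning value.

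Second, 69% is one point in a range that crosses 80%. In ANCOVA, f is scaled by the residual SD, and an unstated correlation near 0.5 with routine baseline adjustment would restore about 80%. This stands as a limit on the figure, but it does not rescue the word conservative: at r = 0.5 the margin is one percentage point. Nor does the article secure that gain. The 12 covariates as described do not include the baseline outcome, and the Data analysis plan adjusts for baseline variables only where they differ significantly between groups.

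Third, the 30% attrition allowance is itself cautious against the cited means. True, yet at those means power is still about 75%. The Data analysis plan also assumes 5% missing data, which would give about 82%, but that conflicts with the 30% used for sizing and is a separate matter. Multiple imputation does not by itself restore lost outcome information.

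A reader might also add the planned Bonferroni adjustment and quote power near 52% (alpha/3). The Data analysis plan names neither the family nor the divisor, and such an adjustment lowers power at f = 0.2 as well (to about 66% at alpha/3). It says nothing about whether f = 0.2 is conservative and should be treated separately.

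**Conclusion.** The justification is wrong as written for depression severity. The planning value d = 0.40 is larger than the cited g = 0.35, so it cannot be conservative against it. It is conservative for insomnia, and for sleep quality the section gives nothing to compare it with.

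At the cited depression effect, power is about 69% on the protocol's own basis: 199 evaluable, alpha 0.05 per outcome, no variance explained by covariates. That is a 31% chance of missing the cited effect, against the 20% a reader would assume. Better retention or routine baseline adjustment would raise it, to the extent shown in the working.

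The stated 199, 285 and 80% at f = 0.2 stand. No estimand, analysis or type I error is affected. This is a correction to a stated justification that should be made, not a fault in the design's arithmetic.

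**What to change.** In the Sample size section:
- Remove the description as conservative for depression, and keep it for insomnia.
- State that 285 randomised (199 evaluable after 30% attrition) gives 80% power at f = 0.2, that is d = 0.40.
- Report that for the cited depression effect of g = 0.35 power is about 69% with 199 evaluable, alpha 0.05 and no variance explained by covariates. Beside it, give the baseline-adjusted figure with the correlation assumed for it.
- Say that no effect for sleep quality was cited, or cite one.

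The effect of the Bonferroni adjustment on power belongs in a separate statement, once the divisor is specified.

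The cost is one paragraph of wording and a less favourable stated power for depression. Recruitment ended in September 2020, and no extra enrolment is proposed.

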### Data analysis plan

The principle of intention-to-treat analysis will be adopted, in which all randomized participants with missing observations, from lost to follow-up or incomplete outcome assessments, will be handled by multiple imputation [53]. Missing data is assumed to be 5%.

Chi-square tests and independent *t* tests will be conducted to examine if participants in the CBT-I and waitlist control conditions differ in terms of demographic characteristics, clinical comorbidity, and baseline outcome scores. Multilevel linear mixed model based on the intention-to-treat principle will be used to calculate between-condition mean differences in the primary outcome changes in sleep quality, insomnia, and depression severity from baseline to post-intervention assessments. Multilevel linear mixed model based on the intention-to-treat principle will also be used to analyze secondary outcomes of the baseline to post-intervention change in subjective health and anxiety between CBT-I and waitlist control conditions. Clustering effect, significant baseline differences in demographics, clinical characteristics, and outcome variables will be adjusted for. Pair-sample *t* tests based on the intention-to-treat principle will be used to analyze changes in primary outcomes, subjective health, and anxiety obtained at post-intervention and 6-week follow-up separately for each condition. All comparisons are planned with a 5% two-sided significance level. Bonferroni adjustment will be applied.

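### The baseline outcome score is adjusted for only if the arms differ significantly, and the N of 199 comes from a different test than the one named, so 80% power is not established for the planned difference in change

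*Protocol article*

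**What the plan says.** **Sample size (Protocol article, Methods).** The calculation for each primary outcome "is based on mixed ANCOVA using GPower 3.1". It is set out as two conditions by two assessments, at two-sided alpha 0.05 with "80% power to detect a small effect of 0.2" (Cohen's f), "while controlling for 12 covariates (demographics, clinical comorbidity, treatment expectancy, and acceptability of treatment". The result is 199, raised to 285 for 30% attrition. The section then says that this detects f = 0.2 "for the difference in the change in each of the three primary outcomes" from baseline to post-intervention. It gives no correlation between the two assessments and does not say which standard deviation f refers to. The outcome's own baseline score is not among the listed covariates.

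**Data analysis plan (same article).** The primary analysis is a multilevel linear mixed model for "between-condition mean differences in the primary outcome changes in sleep quality, insomnia, and depression severity from baseline to post-intervention assessments". On covariates, "significant baseline differences in demographics, clinical characteristics, and outcome variables will be adjusted for", together with any clustering effect. A Bonferroni adjustment is to be applied. The number of tests it covers is not given.

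**The concern.** Two things do not fit together.

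First, the adjustment rule. Participants are allocated by simple 1:1 randomisation, so any baseline difference arises by chance. A significance test on baseline scores does not show whether the baseline score predicts the outcome, which is what decides whether adjusting for it helps. Gating the adjustment on that test lets the primary model vary with the data, possibly from one outcome to the next. In most realisations it also leaves out the covariate most likely to improve precision.

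Second, the power statement. The test named in the sample size section, the calculation that yields 199 and the analysis that is planned are three different things. The power of a difference-in-change test depends on the baseline-to-post correlation, or on f being defined in change-score SDs. The protocol gives neither, so a reader cannot tell what power the planned primary comparison has.

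**Working it through.** **Inputs from the protocol.** f = 0.2, two-sided alpha 0.05, power 80%, two arms at 1:1, 12 covariates, N = 199, attrition 30%. For two equal groups d = 2f = 0.4.

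**Assumed.** The baseline-to-post correlation r is not given and is varied from 0.2 to 0.8. The SD is taken as equal at both assessments. All powers are for 199 completers at two-sided alpha 0.05, before any Bonferroni adjustment.

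**1. Reproducing 199 and 285.** Fixed-effects ANCOVA F test with numerator df 1, denominator df = N − 2 − 12 and noncentrality λ = f²N.
- N = 199: λ = 0.04 × 199 = 7.96, df 1 and 185, power 0.801.
- N = 198: power 0.799.

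So 199 is the smallest N that reaches 80%. The same N results with four cells in place of two groups, or with no covariates. Attrition: 199 / 0.70 = 284.3, rounded up to 285. Both stated figures reproduce.

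**2. The repeated-measures test named in the text.** Condition-by-assessment interaction with two assessments, λ = f²N × 2/(1 − r). The N for 80% power is 101 at r = 0, then 81, 71, 52, 32 and 22 at r = 0.2, 0.3, 0.5, 0.7 and 0.8. The repeated-measures between-group effect, λ = f²N × 2/(1 + r), needs 101, 130, 150 and 169 at r = 0, 0.3, 0.5 and 0.7. None of these is 199. The stated N carries no correlation and treats each participant as contributing one score.

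**3. The planned test at 199 completers.** With one baseline and one post-intervention score, and no baseline adjustment triggered, the between-arm difference in change is a two-group comparison of change scores. The SD of the change is σ√(2(1 − r)). With the baseline score as covariate, the residual SD is σ√(1 − r²). The effective d is then:
- f in single-score SDs: change d = 0.4/√(2(1 − r)); baseline-adjusted d = 0.4/√(1 − r²).
- f in change-score SDs: change d = 0.4 at any r; baseline-adjusted d = 0.4√(2/(1 + r)).

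| r | Change test, f in single-score SDs | Baseline-adjusted, f in single-score SDs | Change test, f in change-score SDs | Baseline-adjusted, f in change-score SDs |
|---|---|---|---|---|
| 0.2 | 60.2% | 81.7% | 80.2% | 95.2% |
| 0.3 | 66.0% | 83.7% | 80.2% | 93.6% |
| 0.4 | 72.7% | 86.5% | 80.2% | 91.9% |
| 0.5 | 80.2% | 90.0% | 80.2% | 90.0% |
| 0.6 | 88.1% | 93.9% | 80.2% | 88.1% |
| 0.7 | 95.2% | 97.6% | 80.2% | 86.1% |
| 0.8 | 99.3% | 99.7% | 80.2% | 84.1% |

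Worked example at r = 0.3 on the single-score scale: change d = 0.4/√1.4 = 0.338, power 66.0%; baseline-adjusted d = 0.4/√0.91 = 0.419, power 83.7%.

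In every row and on either scale, the baseline-adjusted analysis has more power than the unadjusted change test.

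**The case against.** The strongest reply is that the sample size section attaches f = 0.2 to the difference in change. Read literally, f is then in change-score SDs, and a two-group test on change needs 199 at any correlation. On that reading the number suits the planned contrast and only the label is wrong. This stands as a possible reading. It is not the only one: the same section derives f from meta-analytic Hedges' g values without saying which SD applies.

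A reader might infer that the trial is underpowered, or that 80% is simply wrong. The protocol does not support that. On the change-score scale power is 80%. On the single-score scale it is below 80% only for correlations under about 0.5, and above it for higher ones. Nor do the low internal-consistency figures quoted for the PSQI (.59 to .63) point to a low correlation. Cronbach's alpha measures agreement among components at one time, not stability over time.

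Two further replies have some force. In a condition-by-assessment layout, baseline is a level of the repeated factor, so its absence from the 12 covariates is not an omission from that design. And details of a mixed model are commonly left to a statistical analysis plan. The second does not rescue the adjustment rule, because the protocol states the significance condition itself.

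Finally, recruitment is complete, so the sample size part now concerns description only. That is accepted, and no change in N is proposed.

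**Conclusion.** The point holds in two parts.

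The significance-gated adjustment is a poor rule in the current text. It makes the primary model data-dependent and gives up precision that costs nothing to keep. On the single-score scale, adjusting always rather than not at all raises power from 60% to 82% at r = 0.2, and from 80% to 90% at r = 0.5. On the change-score scale it raises 80% to between 84% and 95%.

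The sample size is mislabelled. The figure of 199 belongs to a one-df ANCOVA F test on one score per participant, not to the 2 × 2 condition-by-assessment test. The 80% is therefore not established for the planned difference in change. It may be right, too low or too high, depending on the scale of f and the correlation, neither of which is stated.

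These figures rest on 199 completers, equal SDs at both assessments, the assumed correlations of 0.2 to 0.8, and alpha 0.05 without Bonferroni. How far the Bonferroni adjustment lowers power is a separate question that they do not answer.

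**What to change.** 1. **Data analysis plan.** State that every primary between-arm comparison at post-intervention is adjusted for that outcome's own baseline score, whatever any baseline test shows. Either enter baseline as a covariate or fit a mixed model with baseline means constrained equal across arms. Remove the significance condition for outcome variables.
2. **Sample size.** Describe 199 as a between-group ANCOVA with one numerator df, drop the 2 × 2 mixed ANCOVA wording, and state the SD to which f = 0.2 refers. Give a baseline-to-post correlation only if power is restated for the baseline-adjusted or change analysis, since the calculation behind 199 uses none.

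The cost is two or three sentences. No new data, no extra participants and no change to 199 or 285 are needed. The protocol describes the analyses as still to come; the first change should be recorded before the comparative analysis is run.

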### Recruitment

Participants are recruited on a rolling basis through posters, web-based advertisements, departmental website, social media, and institutional mass mailing. A “proACT-S” Facebook page and a “proACT-S” Instagram account have also been set up for this project, where they contain the recruitment poster and local news articles related to insomnia and depression. Recruitment began in March 2019 and was completed in September 2020.

### Allocation

One week following the completion of the baseline assessment, participants are randomly assigned in a ratio of 1:1 either to the CBT-I group or the waitlist control group using an online randomized algorithm (https://www.php.net/manual/en/function.random-int.php). The group assignment follows the simple randomization procedure and is completely automated to ensure allocation concealment.

### Blinding

The principal investigator is blind to both the outcome assessment and group assignment. The research team is blind to the outcome assessment because all three assessments are self-reported and carried out via the smartphone app, but is not blind to the group assignment as research members need to send emails and WhatsApp reminders to the participants to enhance treatment compliance. Efforts are made to minimize participants’ knowledge of treatment allocation by informing participants that the treatment start date is randomly assigned. Statistical analyses will be carried out by a researcher blind to the study protocol. In the unlikely event of a critical incident, the research team, as well as the principal investigator, will be authorized to break the blind and carefully record it on the Case Report Form.

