### Participant timeline

Individuals interested in participating are invited to complete a two-stage screening. In stage 1 online rapid screening, they complete an online survey to review their eligibility. Those who have passed the online rapid screening will receive a link within the Qualtrics platform to sign up for the stage 2 telephone diagnostic interview screening. These telephone interviews are conducted by project assistants, who have been trained and supervised on the administration of the modified Chinese version of the CIS-R [34].

Individuals who do not meet the stage 2 telephone diagnostic interview screening eligibility criteria will receive a list of references related to insomnia and depression produced by the Department of Health and the Social Welfare Department under the Government of the Hong Kong SAR. Information regarding crisis hotlines and integrated community centers for mental wellness are provided to those currently with suicidal plans or acts, or those who have had suicidal plans or acts within the past 12 months.

Individuals who have passed the two-stage screening are directed to download proACT-S either from App Store or Google Play. Eligible participants are guided to register for their own personal accounts to enter the main study trial. They then complete the baseline assessment via proACT-S. After that, they are randomly assigned in a 1:1 ratio either to CBT-I condition or waitlist control condition.

Participants in the CBT-I condition start the 6-week CBT-I immediately after randomization, complete the post-intervention assessment right after they finish the treatment, and complete the follow-up assessment 6 weeks after the post-intervention assessment. Participants in the waitlist control group wait for 6 weeks without the proACT-S intervention and then complete the post-intervention assessment 6 weeks after the baseline assessment. The waitlist control participants start CBT-I (equivalent to that of the CBT-I group) immediately after completing the post-intervention assessment, and they complete the follow-up assessment right after finishing the 6-week CBT-I.

Emails and WhatsApp reminders are sent to participants to increase their engagement and to enhance treatment compliance. Upon completion of the study, each eligible participant receive cash coupons of HKD $100 as a token of appreciation for their participation. The proposed flow of participants is displayed in Fig. 2.

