### Ethics and dissemination

Consent is obtained electronically for the stage 1 online rapid screening, verbally for the stage 2 telephone diagnostic interview screening, and via the smartphone app proACT-S for the 6-week CBT-I intervention. The consent form explains that participation is voluntary; individuals could withdraw from the study at any time without any consequences.

Participants directly enter their data via Qualtrics during the stage 1 online rapid screening and via proACT-S during the main trial study. Manual data entry from trained project assistants (i.e., telephone interviewers) is required for recording participants’ stage 2 telephone diagnostic interview screening data. A Qualtrics survey based on the modified Chinese version of the CIS-R [34] was created to enable data entry, coding, and storage, in addition to standardizing the administration of the stage 2 screening across different trained telephone interviewers. Participants’ personal data are sent to the electronic server located at The University of Hong Kong and protected using dual encryption. The principal investigator and the research team are given access to the dataset. Participants’ research files may be reviewed by the Human Research Ethics Committee of the University of Hong Kong in order to check that the study is being carried out correctly. Participants will not be identified by name in any report of the completed study. Their personal data will be kept for five years after the publication of the first original research paper, and research data without personal identifiers will be stored for long term retention at the Community Action Research Laboratory at The University of Hong Kong.

This protocol will be published in an open-access journal for public access. Researchers interested in using the de-identified dataset to test novel hypotheses could contact the corresponding author and submit a data proposal form to be reviewed by the research team. The study findings will be disseminated in peer-reviewed publications and conference presentations. Executive summaries will be made available on the proACT-S project website and disseminated to other organizations such as the funding agency and local news agencies.

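### The analyst is said to be blind to the protocol, and blinding of the analyst to group assignment is stated nowhere

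*Protocol article*

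**What the plan says.** The Blinding section takes the parties in turn.

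- Principal investigator: "The principal investigator is blind to both the outcome assessment and group assignment".
- Research team: blind to the outcome assessment, "but is not blind to the group assignment as research members need to send emails and WhatsApp reminders to the participants".
- Participants: their awareness of allocation is to be limited by telling them that the start date is random.
- Analyst: "Statistical analyses will be carried out by a researcher blind to the study protocol".

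The analysis itself is set out in the same article, under Data analysis plan. The primary analysis reads: "Multilevel linear mixed model based on the intention-to-treat principle will be used to calculate between-condition mean differences in the primary outcome changes", from baseline to post-intervention. Missing observations are to be multiply imputed, and paired tests within each condition cover the later change. On covariates the plan says: "Clustering effect, significant baseline differences in demographics, clinical characteristics, and outcome variables will be adjusted for".

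On data access, Ethics and dissemination says: "The principal investigator and the research team are given access to the dataset". Coded arms and a masked analysis file are not mentioned there or elsewhere.

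**The concern.** Blinding an analyst normally means hiding which arm is which, so that modelling decisions cannot be steered by the direction of the result. The analyst is expected to know the protocol, because it says what to do. The sentence here reverses this: it hides the protocol and does not mention the arm.

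Two things are at stake. One is coherence, since a person kept from the protocol is expected to carry out an analysis that is part of it. The other is protection against bias. The covariate set is not fixed in advance under Data analysis plan. It depends on which baseline variables differ significantly between the arms, and someone has to run those comparisons, decide what counts as a clinical characteristic and settle the final model. An analyst who knows the arms could make those decisions with the treatment effect in view.

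**Working it through.** The point concerns who is blind to what, so the check is mainly a comparison of passages.

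**Step 1. The plan's own figures, to see whether any depends on the sentence.** Inputs from Sample size: Cohen's f = 0.2, two groups, 12 covariates, alpha 0.05 two-sided, 80% power, 30% attrition. For an ANCOVA F test with 1 numerator degree of freedom, the denominator degrees of freedom are N − 2 − 12 and the noncentrality is f² × N. At N = 199 these are 185 and 0.04 × 199 = 7.96. Power is 0.801, and 199 is the smallest N that reaches 0.80. For attrition, 199 / 0.70 = 284.3, rounded up to 285. Both stated figures reproduce. Who is blinded enters neither calculation, so correcting the sentence changes no N, alpha or power.

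**Step 2. What is concealed from whom.**

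| Party | Group assignment | Outcome assessment | Protocol |
|---|---|---|---|
| Principal investigator | blind | blind | not mentioned |
| Research team | not blind | blind | not mentioned |
| Participants | knowledge minimized | they report it themselves | not mentioned |
| Analyst | not mentioned | not mentioned | blind |

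The analyst is the only party for whom the protocol is concealed, and the only one for whom group assignment is not addressed.

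**Step 3. The sentence against the Data analysis plan.** The imputation approach, the mixed model, the primary contrast and the covariate rule are all part of the protocol. An analyst blind to it would need those instructions by another route. The article names none.

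**Step 4. Where masking would matter.** The adjustment rule requires between-arm comparisons of baseline variables before the model is settled. With arms coded A and B, those comparisons can still be made, but the analyst does not know which choice favours the intervention.

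**Step 5. Whether coded labels would be enough.** Table 2 shows these collection patterns:

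| Field | Baseline | Post-intervention | 6-week follow-up |
|---|---|---|---|
| Expectancy | both arms | CBT-I only | waitlist only |
| Acceptability | both arms | CBT-I only | waitlist only |
| Contamination check | neither | waitlist only | waitlist only |

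A file holding the post-baseline values would reveal the arm through which cells are filled, even with A/B labels. The baseline expectancy and acceptability scores would not, since both arms supply them.

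**Step 6. Fit with the covariates in the sample size section.** That section counts expectancy and acceptability among the 12 covariates. At post-intervention only the CBT-I arm has these scores, so they could not serve as covariates in a between-arm model. The baseline scores could. Removing only the post-baseline values is therefore compatible with that covariate list.

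**The case against.** The best defence is that the sentence describes what the analyst knows and does not say that the analyst receives no instructions. A separate analysis plan or written specification could carry everything needed, and one may exist although it is not shown. Ignorance of the hypotheses may also limit bias, and the wording may simply be a slip for group assignment. Outcomes are self-reported through the app and randomization is automated, so the analyst can affect neither. All of this stands, and it limits what can be claimed.

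A reader might go further and infer any of the following. The documents do not support them.

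- *The planned analysis cannot be followed.* Another document could convey it. Because the plan is published, departures from it can also be checked.
- *The analyst sees the arms, so bias is uncontrolled.* The article does not say this. It only fails to say that the analyst is blind to assignment.
- *The analyst might treat the follow-up visit as a controlled comparison.* It is not one for the waitlist arm, since "they complete the follow-up assessment right after finishing the 6-week CBT-I". But the Data analysis plan already confines the between-arm contrast to baseline and post-intervention, and gives follow-up only within-condition tests.
- *The multiplicity correction becomes open.* The plan says "All comparisons are planned with a 5% two-sided significance level. Bonferroni adjustment will be applied" without naming the family of tests. An analyst holding the protocol would face the same gap, so it is a separate question.
- *Power is lost.* Any such figure would rest on an analyst disregarding the stated contrast or on the size of the Bonferroni family. Neither measures the bias that masking is meant to prevent.

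The defence does not rescue the sentence itself. A separate plan could supply the instructions, but it would not turn blindness to the protocol into blindness to allocation. If the wording is a slip it needs correcting, and if it is intended it conceals the wrong thing.

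**Conclusion.** The point holds as a defect in a stated rule. The article names the protocol as what the analyst must not know, and nowhere says that the analyst is blind to group assignment. Taken literally, the sentence conflicts with carrying out the pre-specified analysis, and it does not assure protection against analyst bias. The practical relevance comes mainly from the covariate rule, which depends on observed differences between arms.

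The conclusion rests on the article's text alone and assumes no unseen document already states that the analyst is blind to allocation. It does not claim that the analysis was or will be biased, or that the plan cannot be carried out. No numerical size can be attached. The sentence should be corrected, in proportion to a cheap safeguard that is currently not stated.

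**What to change.** Replace the sentence under Blinding with: *The statistician works from the pre-specified protocol and analysis plan and is blind to treatment allocation; arms are coded A/B until the primary models are final.*

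For the primary baseline-to-post analysis, supply a dataset without the fields whose presence reveals the arm: the contamination check, and the post-baseline expectancy and acceptability scores. Keep the baseline expectancy and acceptability scores, so that the covariates named under Sample size can still be used and the masking is reconciled with that list. The withheld fields can be released once the primary models are final.

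The cost is one sentence and a small amount of data-management work to prepare the coded export. Masking does not make the covariate rule any less data-driven; it only keeps the choice from being made with the direction of benefit known.
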